## Ethical considerations

All participants are offered treatment as usual, i.e. treatment according to best practice and adapted to the individual needs of the patient. The trial will follow the international ethical guidelines of informed consent in clinical trials. Consent will be voluntary, informed and given both verbally and in writing. The participants will be informed about their rights to decline participation or to withdraw with no consequences to their future care or treatment. The participants will not receive a fee for their participation.

Signed consent forms will be dated, with a copy being given to the participant, and the original form kept with the research data in a locked filing cabinet. The trial has been reviewed and approved by The Ethics Committee in the Capital Region of Denmark (registration number H-1-2010-134), it is reported to the Danish Data Protection Agency and it is registered at http://www.clinicaltrials.gov (number NCT01361698).

Previous research does not indicate that IMR induces risk to the participating patients. All adverse events e.g. increase in symptoms, decrease in functioning, changes in alcohol/drug consumption and incidents of suicide, and also all beneficial events e.g. increase in level of function, hope or progress in recovery will be registered and reported. Participating in the Present State Examination, baseline and follow up interviews may cause some disturbance to the participants, but will be planned flexibly with possible breaks when needed. The results from this trial will contribute with evidence to improve treatment and rehabilitation of people diagnosed with schizophrenia and bipolar disorder. The results will also contribute to future evidence in relation to the IMR program. In the opinion of the research team the pros greatly counterbalance the cons in this trial.

## Discussion

The IMR trial is a randomised clinical trial to evaluate the effectiveness of the IMR-program for people diagnosed with schizophrenia and bipolar disorder in according to their level of functioning.

In this design of testing the IMR program an important factor is to insure the fidelity to the IMR program curriculum, so that the IMR program is the taught the same way, using the same slides and same topic areas across the participating community mental health centres. A strength of this trial is therefore that all IMR facilitators go through a specific course of education prior to the intervention, have profound supervision during the intervention and that we test the fidelity using the IMR fidelity scale throughout the course of each IMR group.

Another strength in the design of this trial is that a solid sample size calculation has been made, so we will be able to perform a data analysis with good strength according to the primary outcome, GAF-F. Besides this we have estimated the power of some the secondary measures with a total number of 200 participants. This showed that a sample size of 200 participants is sufficient to show a relevant effect size in the secondary outcome measurements PSP, PANSS and the IMR Scale which will strengthen the results in these aspects. Furthermore, the risk of selection bias related to allocation sequence generation and concealment is low, as the randomisation is performed centrally according to a computer-generated allocation sequence generation. The fact that the assessor of the primary outcome is blinded and that intention-to-treat analysis are going to be used as a statistically approach in the data analyses are also strengthening the design of this trial.

Some would argue that that there is a difference between the level of functioning of the two diagnoses, which is seen in studies comparing level of functioning for in-patients, though literature about this issue is inconsistent in their conclusions [41-43]. A recent study from Norway comparing Global Assessment of Function for the diagnoses schizophrenia and bipolar disorder in a mixed study population of in-patients and out-patients conclude that schizophrenia and bipolar disorder cannot be viewed as categorically different [44]. In the design of this trial we have carefully considered this aspect and have chosen to mix patients with two the diagnosis, since there some support of an equal level of functioning on the GAF score (it ranges from 51.79 to 53.00) [24,38,45] for this trial population and since patients included in the trial are admitted to the same treatment unit reflected same level of functioning. However, to secure that the compared groups are similar the allocation sequence is stratified by diagnosis and community mental health centre. This way potential difference in prognostics features between the two diagnoses and community mental health centres are accounted for, which increase the validity of comparison between the intervention and control group.

A limitation in the design of this trial is that some of the staff members both are IMR facilitators and at the same time maybe have patients that get treatment as usual. We have chosen not to force the patients to change their primary care provider after the result randomisation. This demands that the staff members have a stringent separation of what is the treatment as usual and what is treatment methods according to the IMR concept. To handle situation where staff might be confused of they are mixing the IMR concept with treatment as usual they can consult a task force consisting of a well-experienced psychiatrist only performing treatment as usual.

A limitation to the trial design is that only the assessor rating the factors associated to the aspects of clinical recovery is blind to allocation. When investigating a rehabilitation program like IMR it is not possible to blind the participant or the staff, so this might increase bias. The risk of bias could be seen according to the assessments related to personal recovery which is rated both by the primary care provider and by the participating patient since the awareness of the currently treatment might bias the outcome. On the other hand we think it is strength of this trial that we both get a subjective view of recovery when the person in recovery are to evaluate his/her own process and a more objective view with the clinical assessment from the primary care provider which have fulfilling knowledge of the patient though close contact.

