### Recruitment and randomisation

Patients will be recruited from two community mental health centres in the Capital Region of Denmark: Frederiksberg-Vanløse and Ballerup-Egedal-Herlev, respectively. Each potential participant is interviewed with the diagnostic tool Present State Examination by a psychiatrist or a trained psychologist to evaluate whether the patient meets the criteria of diagnosis. After informed consent is obtained for each eligible patient the baseline assessments will be conducted. After baseline assessments the participants will be randomly allocated to either IMR or continue with treatment as usual. To secure concealment of the allocation sequence the randomisation will be central and telephone-based through The Copenhagen Trial Unit. The allocation sequence will be computer-generated, using permuted blocks of a varying block size with equal allocation to the two arms. The allocation sequence is stratified by diagnosis and community mental health centre.

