## Analysis

### Power and sample size

We are planning a trial of the continuous response variable, GAF-F, from independent control and experimental participants with one control per experimental participant. A previous study involving psycho-education in a Danish community mental health centre showed that response within each participant group was normally distributed with a standard deviation of 15 [38]. In the few previous studies using IMR or elements of IMR the effectiveness has been assessed by using the total GAF score showing a difference of 6-10 points [21,39]. Based on this knowledge we will conservatively estimate the true difference in the experimental and control group means to be 6 points on the GAF-F score. Using this estimation will require a total of 200 participants to reject the null hypothesis that the population means of the experimental and control groups are equal with probability (power) 0.8. The type I error probability associated with this test of the null hypothesis is 0.05. The power and sample size calculations have been made using the PS Power and Sample Size Calculations program version 3.0.34 [40].

The power of some the secondary measures has also been estimated with a total number of 200 participants. This showed that a sample size of 200 participants is sufficient to show a relevant effect size in PSP, PANSS and the IMR Scale corresponding to similar studies, see table 2. The remaining secondary measures have not been tested due to the fact that similar trials with these outcomes could not be obtained. Thus, the results of these analyses should be interpreted with caution, and the analyses should be considered as exploratory.

**Table 2 T2:** Power calculations of PSP, PANSS and IMR Scale

Measure	The level of significance	Power	St. deviation in a similar study	Effect size in a similar study	Minimum sample size	Reference
PSP	0,05	0,8	14	7	128	*Nasrallah et al. 2008 *[40]

PANSS	0,05	0,8	11	5	154	*Fowler et al. 2009 *[41]

IMR scale	0,05	0,8	0,5	0,41	48	*Hasson-Ohayon et al. 2007*[17]

Note: PSP: Personal and Social Performance; PANSS: Positive and Negative Syndrome Scale; IMR Scale: Illness Management and Recovery Scale.

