## Data analysis

The analysis will be performed by using the IBM SPSS Statistics version 19 for Windows. The data analysis will be based on the principle of intention-to-treat. The significance level for the analysis of the primary outcome and the secondary outcome will be 0.05.

Demographic variables will be listed in a table. The primary outcome measure is the continuous measurement GAF-F. The primary analysis of effectiveness will compare GAF-F at 9 months. The secondary analysis will compare effectiveness of the secondary outcome measures at 9 months and GAF-F and the secondary outcomes at 21 months. The analysis of differences between groups will be conducted using t-tests and analysis of the variances will be conducted using ANOVA. Repeated measures techniques may also be applied. Dichotomous outcome assessments will be analysed using logistic regression and paired dichotomous outcomes will be analysed using McNemar tests, or using logistic regression with random effects. Missing data is a potential source of bias and therefore the operation of multiple imputations will be used to address the issue of missing values. An analysis of the drop-out will be conducted to validate the complete case analyses.

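### Randomisation is stratified by diagnosis and centre, but the stated group comparison is an unadjusted t-test, which is conservative to the extent that the strata predict outcome

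*Protocol article*

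**What the plan says.** - **Recruitment and randomisation:** patients are allocated 1:1 in permuted blocks of varying size. "The allocation sequence is stratified by diagnosis and community mental health centre". With two diagnoses and two centres this makes four strata.
- **Data analysis:** "The analysis of differences between groups will be conducted using t-tests". ANOVA is named as well, but without factors. Repeated measures methods are left optional, and logistic regression is named for dichotomous outcomes. Neither diagnosis nor centre is named in any model.
- **Monitoring for participant compliance:** covariates are said to be recorded, but they are not named or tied to a model.
- **Discussion:** the stated aim of stratifying is to make the compared groups similar, and the benefit is put as follows: "This way potential difference in prognostics features between the two diagnoses and community mental health centres are accounted for". The same paragraph cites GAF levels from 51.79 to 53.00 as some support for equal functioning in the two diagnoses.

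**The concern.** Stratified blocks hold diagnosis and centre nearly equal between the arms. Whatever part of the outcome these factors explain therefore drops out of the sampling variation of the treatment difference. A two-sample t-test does not know this. It estimates its standard error from the total variance within each arm, which still contains the variation between strata. If the factors are prognostic, the confidence interval is wider than the design warrants, the p-value is too high, and part of the precision gained by stratifying is not used.

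What is at stake is efficiency and agreement between the nominal and actual error rate. Validity is not at stake: the difference in means remains unbiased and the error is on the conservative side.

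**Working it through.** **Inputs from Power and sample size**
- Difference: "conservatively estimate the true difference in the experimental and control group means to be 6 points on the GAF-F score".
- Spread: "response within each participant group was normally distributed with a standard deviation of 15".
- Allocation: "with one control per experimental participant".
- Significance level: "The type I error probability associated with this test of the null hypothesis is 0.05". Sidedness is not stated.
- Power: the null hypothesis is to be rejected "that the population means of the experimental and control groups are equal with probability (power) 0.8".

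**Step 1: the plan's own figure.** Two-sided, n per arm = 2 × (1.960 + 0.842)² × 15² / 6² = 98.1, rounded up to 99, or 198 in total. This agrees with the stated 200. A one-sided test would need 156, so two-sided is taken. At 100 per arm the standard error is 15 × √(2/100) = 2.121, and power is Φ(6/2.121 − 1.96) = Φ(0.868) = 0.807 (0.804 with the noncentral t). The sample size is not in question here.

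**Step 2: effect of ignoring the strata.** Let R² be the share of outcome variance explained by the four strata. The article does not give it, so a range is assumed. Under stratified 1:1 allocation the true standard error is about 2.121 × √(1 − R²), while the t-test reports about 2.121. Hence:
- Ratio of reported to true standard error = 1/√(1 − R²)
- Actual level of the nominal 5% test = 2 × [1 − Φ(1.96/√(1 − R²))]
- Power, t-test = Φ(0.868/√(1 − R²))
- Power, adjusted model = Φ(2.828/√(1 − R²) − 1.96), where 2.828 = 6/2.121

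| R² (assumed) | SE too large by | Actual level | Power, t-test | Power, adjusted |
|---|---|---|---|---|
| 0.0016 | 0.1% | 4.98% | 0.808 | 0.808 |
| 0.05 | 2.6% | 4.4% | 0.814 | 0.827 |
| 0.10 | 5.4% | 3.9% | 0.820 | 0.847 |
| 0.20 | 11.8% | 2.8% | 0.834 | 0.885 |

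Worked row, R² = 0.10: √0.90 = 0.949; 1/0.949 = 1.054; 1.96/0.949 = 2.066, which gives a level of 0.039; Φ(0.868/0.949) = 0.820; Φ(2.828/0.949 − 1.96) = 0.847.

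**Step 3: which R² is plausible for GAF-F?** If diagnosis alone mattered, with a 50:50 mix and total SD 15, a difference of d points gives R² = (d/2)²/225.
- The article's only figure is 53.00 − 51.79 = 1.21 points, so R² = 0.605²/225 = 0.0016.
- Assumed differences of 5 and 10 points give R² of about 0.03 and 0.11.
- Conversely, R² of 0.05, 0.10 and 0.20 would need differences of 2 × 15 × √R² = 6.7, 9.5 and 13.4 points.

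The 1.21 points are a range across cited studies, not a contrast between the diagnoses. No centre effect is given.

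**Step 4: simulation.** The setting was 200 participants, four equal-probability strata, permuted blocks of 4 and 6 (assumed sizes) and 10,000 runs per setting. The t-test was compared with a linear model containing stratum terms.

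| R² | Type I error, t-test / adjusted | Power, t-test / adjusted |
|---|---|---|
| 0.0016 | 0.052 / 0.052 | 0.807 / 0.807 |
| 0.05 | 0.040 / 0.045 | 0.810 / 0.826 |
| 0.10 | 0.036 / 0.048 | 0.813 / 0.841 |
| 0.20 | 0.027 / 0.046 | 0.827 / 0.882 |

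The simulation standard error of a 5% rate is √(0.05 × 0.95/10,000) = 0.002. The pattern agrees with the formulas up to about that noise.

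**The case against.** - **A contradiction with the Discussion.** A reader might infer that the Discussion promises an analysis that allows for diagnosis and centre, and that the t-test breaks this promise. The text does not support that. The sentence follows directly on the aim of making the groups similar, so it concerns balance, which stratified blocks deliver. It says nothing about standard errors or models.
- **Certainly wrong p-values, or precision lost altogether.** This too would go beyond the documents. The mismatch exists only if the strata predict outcome, and the one GAF range available implies practically no effect from diagnosis. Part of the benefit is also kept: the t-test's own power rises with R², from 0.808 to 0.834 over the range shown, and never falls below the planned 80% when all 200 are analysed.
- **Larger effects elsewhere.** Diagnosis may well matter more for PANSS or the Young Mania Rating Scale, and centre for service use. The article gives no figure for any of these, so this remains a possibility and not a result.
- **Left to the analysis plan.** The article is a condensed text, and its covariate list may stand in an analysis plan that is not shown. This has weight, but it does not remove the point. The article names a specific method, and that method cannot carry the factors. An adjusted analysis would depart from the published statement.

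**Conclusion.** The point holds as an efficiency matter. The trial randomises within strata and states a comparison that does not use them. If the strata explain 5% to 20% of outcome variance, the reported standard error is 2.6% to 11.8% too large, the actual level of the 5% test is 4.4% down to 2.8%, and adjustment would raise GAF-F power by about 1 to 5 percentage points. If they explain about 0.16%, nothing changes.

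The figures rest on an assumed R², SD 15, a 6-point difference, a two-sided test and all 200 participants analysed. There is no bias, no inflated type I error and no shortfall against planned power under these assumptions. The change is still worth making because it costs almost nothing and protects against strata that turn out to be prognostic.

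**What to change.** In Data analysis, replace the t-test for GAF-F and for the continuous secondary outcomes with a linear model (ANOVA or ANCOVA) that has treatment, diagnosis and centre as fixed factors. This uses about two degrees of freedom out of about 200 (196 residual instead of 198), and both factors are known at randomisation, so no new data are needed.

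For dichotomous outcomes, put the same two factors in the logistic model and state that the odds ratio is then conditional on them. This is more than a change of wording, because the adjusted odds ratio is a different quantity from the unadjusted one.

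The Discussion sentence is correct as a statement about balance and can stay as it is.
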